### Primary outcomes

The primary endpoint will be the proportion of patients achieving a ≥15% reduction in serum alkaline phosphatase (ALP) and gamma-glutamyl transferase (GGT) levels at 3, 6 and 12 months compared with the one-month post-transplant baseline between the two groups. ALP and GGT is assessed at 6 and 12 months to evaluate the trajectory and durability of response over time.

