**Blinding**

This is an open-label study. Blinding is not feasible due to the nature of the interventions. Given the difference in tablet size and dosing frequency (three times daily for UDCA vs once daily for OCA), blinding is not being done.

Primary outcomes will be based on objective biochemical parameters to minimize bias.

Given the difference in tablet size and dosing frequency (three times daily for UDCA vs once daily for OCA), blinding is not being done.

Follow-up visits for physical examinations and safety assessments are being scheduled during the study period at the following intervals: one month, three months, six months, and twelve months post-transplant (
Figure 1).

Study assessments were initiated at one month post-transplant because a substantial proportion of our liver transplant recipients are high-MELD patients who often have markedly elevated bilirubin and cholestatic enzyme levels in the immediate postoperative period. In addition, transient elevations in liver function tests are commonly observed during the early post-transplant phase due to ischemia–reperfusion injury, surgical factors, sepsis, or early graft dysfunction or rejection.

In live donor liver transplantation, particularly among high-MELD recipients, these fluctuations are often pronounced during the first few weeks after surgery. Therefore, a four-week stabilization period was allowed to enable resolution of early postoperative variability and to ensure that subsequent biochemical measurements more accurately reflect the effects of the study intervention rather than perioperative factors.

Liver function tests, C-reactive protein (CRP), platelet count, prothrombin time/international normalized ratio (PT/INR), fasting blood sugar (FBS), tacrolimus concentration, and other relevant parameters are being measured at each follow-up visit. Lipid profile—including total cholesterol, low-density lipoprotein (LDL), high-density lipoprotein (HDL), very low-density lipoprotein (VLDL), and triglycerides (TG)—as well as glycosylated hemoglobin (HbA1c) levels, are being assessed at pre-transplant admission, and at three, six, and twelve months post-transplant.

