### Statistical analysis

•To compare the means of continuous variables between groups (Drug A vs Drug B), an independent sample t-test will be used at each time point.•To compare the changes in continuous variables from pre- (1 month) to post-transplant (3, 6, and 12 months), a paired t-test will be applied.•To compare the means of variables from baseline to subsequent time points within each group, repeated measures ANOVA will be used if significant. Repeated measures analysis will be used to assess longitudinal changes over time, and Bonferroni correction will be applied for multiple comparisons where appropriate.

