## Expected results

We expect a significant reduction in cholestatic liver enzymes following LDLT in the OCA group compared to the UDCA group, with improvements observed from one month to subsequent time points (3, 6, and 12 months). We hypothesize that the potent mechanism of action of OCA will ameliorate cholestatic injury and enhance graft survival. Additionally, we anticipate a reduction in biliary complications, all-cause mortality, and an increase in quality of life for OCA-receiving patients. This may reduce long-term financial expenditure for patients. Given that there are currently no drugs to prevent damage to the transplanted liver, a positive outcome could be a significant advancement for the transplant population. If beneficial, this study could lead to the adoption of OCA as a standard of care following liver transplantation. If proven beneficial, this study could support the potential adoption of obeticholic acid (OCA) as a therapeutic option in the management of post-liver transplant cholestasis. Although regulatory approval for OCA in primary biliary cholangitis was withdrawn due to the lack of confirmatory clinical benefit, its distinct mechanism of action and the different pathophysiological context of post-transplant cholestasis warrant independent evaluation in this setting.

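### The planned tests of change from month 1 contain no OCA–UDCA contrast, and one of them runs only on an undefined condition

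*Protocol article*

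**What the plan says.** All references are to the protocol article.

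- **Primary outcomes** sets a between-group question about change from month 1, assessed at the three later visits: "The primary endpoint will be the proportion of patients achieving a ≥15% reduction in serum alkaline phosphatase (ALP) and gamma-glutamyl transferase (GGT) levels". Expected results likewise anticipates a larger enzyme reduction with OCA than with UDCA, with improvement after month 1.
- **Statistical analysis**, first bullet, compares the two drugs: "an independent sample t-test will be used at each time point".
- The second bullet covers change over time: "from pre- (1 month) to post-transplant (3, 6, and 12 months), a paired t-test will be applied". No arm comparison is attached.
- The third bullet covers change from baseline: "within each group, repeated measures ANOVA will be used if significant". What has to be significant is not stated.
- A closing sentence adds: "Repeated measures analysis will be used to assess longitudinal changes over time, and Bonferroni correction will be applied for multiple comparisons where appropriate". It names neither an arm term nor an arm-by-visit term.
- **Blinding** notes that "transient elevations in liver function tests are commonly observed during the early post-transplant phase", and says that four weeks were allowed for these to settle before measurement began.
- **Allocation** has the envelopes opened on postoperative day two, so the month-1 value is measured after randomisation.

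**The concern.** A test of change inside one arm asks whether that arm moved. It does not ask whether OCA moved it more than UDCA did. In a population recovering from surgery, both arms may improve after month 1 for reasons unrelated to either drug. A significant fall under OCA beside a non-significant fall under UDCA is then easily read as a drug effect, although the two falls may not differ.

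The conditional wording adds a second problem. An analysis run only after some unnamed result is significant is not prespecified, and its p-value has no clear interpretation. At stake is a claim of OCA benefit on enzyme change that rests on no randomised contrast of change.

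**Working it through.** **1. Match each listed method to the question.**

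| Method in Statistical analysis | Compares arms? | Addresses change from month 1? |
|---|---|---|
| Independent t-test at each visit | Yes | No, levels only |
| Paired t-test, month 1 vs 3, 6, 12 | No | Yes |
| Repeated measures ANOVA in each group | No | Yes, but conditional |
| Closing repeated measures sentence | Not stated | Yes |

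No method is stated to do both, which is what Primary outcomes asks for. Whether the paired test is run per arm or on pooled patients makes no difference: neither version contains an arm contrast.

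**2. How often can within-arm tests mislead?**

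Inputs: 108 per arm (Sample size section). Assumed: the same true change in both arms; normally distributed changes with SD 1; two-sided 5% tests; one follow-up visit; standardised change δ of 0.2, 0.3 or 0.5. The protocol gives no value for δ. The 108 is used only as the arm size. It does not follow from the printed pilot figures (difference 12.496 − 5.131 = 7.365, pooled SD 46.31, which need 621 per arm for 80% power at two-sided 5%), but that is a separate matter and does not affect this check.

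The paired test has noncentrality δ√108, which is 2.08, 3.12 and 5.20. With power p in each independent arm, the chance that exactly one arm is significant is 2p(1 − p). A simulation of 20,000 trials per scenario gave:

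| δ | p per arm | 2p(1 − p) | Simulated: exactly one arm | Simulated: OCA only | Between-arm test of change rejects |
|---|---|---|---|---|---|
| 0.2 | 0.542 | 2 × 0.542 × 0.458 = 0.496 | 49.6% | 24.5% | 5.1% |
| 0.3 | 0.871 | 2 × 0.871 × 0.129 = 0.225 | 22.4% | 11.1% | 4.9% |
| 0.5 | 0.9995 | 2 × 0.9995 × 0.0005 = 0.001 | 0.1% | 0.06% | 4.9% |

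The maximum of 2p(1 − p) is 0.50, at p = 0.5, so the first row is close to the worst case.

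**3. Where might this trial lie?**

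The last sentence of Sample size suggests that the pilot ALP figures are reductions. If so, the standardised changes are 5.131/39.639 = 0.13 and 12.496/52.139 = 0.24. These lie on either side of 0.2, where discordance is high. This is only indicative, because the protocol does not say outright that the figures are changes and does not give the pilot's size.

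**The case against.** The strongest reply is that the plan does compare the arms. The visit-wise independent t-test is a randomised comparison, and recovery common to both arms cancels out of it. This stands. A reader might infer that the whole plan fails to estimate the OCA–UDCA difference, or that all its tests confuse recovery with drug effect. The first bullet refutes that. Its limits are that it is unadjusted, which costs precision and not validity, and that it compares levels.

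Second, nothing in the protocol says that benefit will be inferred from significance in one arm only, and the within-arm tests could be meant as description. That is fair. But they carry p-values, and they are the only fully specified methods for change.

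Third, the four-week stabilisation period is there to let early fluctuation settle. It makes large shared recovery after month 1 less likely without excluding it, so the documents do not establish that both arms will improve regardless of drug. Large shared recovery would also make both paired tests significant, as the row for δ = 0.5 shows.

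Three further inferences are not supported:

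- **Log transformation because the pilot SDs far exceed the means.** The figures appear to be reductions, and an SD larger than a mean change says nothing about skewness of the raw enzymes. No pilot GGT figures are given.
- **A quantified precision gain from baseline adjustment of ALP and GGT.** Liver function tests are listed at follow-up visits only. No pre-randomisation ALP or GGT is described, and its correlation with later graft values is unknown.
- **A quantified loss of patients from complete-case ANOVA.** The protocol gives no missing-visit rate.

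**Conclusion.** The point holds for the methods that address change. The paired t-test and the within-group ANOVA give no OCA–UDCA contrast, the ANOVA hangs on an undefined condition, and the one explicit between-arm test does not address the change that the primary outcome is built on.

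With 108 per arm and equal true change, significance in exactly one arm occurs in about half of trials at a standardised change of 0.2, about 22% at 0.3 and almost never at 0.5, against about 5% for a between-arm test of change. These figures rest on the assumed changes and on normality. The defect should be corrected before analysis. It does not invalidate the visit-wise t-tests.

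**What to change.** 1. For ALP, GGT and other markers measured at several visits, make the continuous-outcome analysis one between-arm mixed model for repeated measures with arm, visit and arm-by-visit terms. Use all available data from randomised patients, and report the OCA–UDCA difference with a 95% confidence interval at each visit. If month 1 is included as an outcome visit, the between-arm difference in change from month 1 is a contrast of the same model.
2. Do not use month 1 as a pre-treatment covariate, because it follows allocation. Add a pre-randomisation enzyme value only if hospital records hold one.
3. Report within-arm changes descriptively, without p-values, and delete the conditional wording from the ANOVA bullet.
4. For the CLDQ, use ANCOVA at 12 months adjusted for the pre-transplant score, which the Quality of life section already collects.
5. State that this model supports, and does not replace, a between-arm analysis of the binary primary endpoint.

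The cost is analysis wording and code. Retrieving a pre-randomisation enzyme value would be optional extra work. Using all available data also means reconciling this analysis with the Eligibility section, which excludes patients lost to follow-up. The trial is still recruiting, so the change can be made in time.

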### Sample size

The sample size was calculated based on a pilot study comparing the effect of obeticholic acid (OCA) and ursodeoxycholic acid (UDCA) on cholestatic injury in post-liver transplant patients. In the pilot study, the difference in alkaline phosphatase (5.131 ± 39.639 vs 12.496 ± 52.139) was observed between the two groups. With 80% power and 95% confidence, the minimum sample size required was determined to be 108 patients in each group, totaling 216 samples. We will be recruiting around 110 to 120 patients per arm. The calculation was based on the expected difference in ALP reduction between groups observed in pilot data.

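### Cheap improvement: wherever the plan applies its Bonferroni correction, Holm's step-down version gives the same family-wise 5% control and is never less powerful

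*Protocol article*

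**What the plan says.** The Statistical analysis section of the protocol article has three bullets. The first covers comparisons between the arms: "an independent sample t-test will be used at each time point". It names no correction. The second plans paired t-tests of change from month 1. The third opens with comparisons inside each arm: "To compare the means of variables from baseline to subsequent time points within each group, repeated measures ANOVA will be used if significant". It then adds "Repeated measures analysis will be used to assess longitudinal changes over time", and that same sentence ends with the only statement on multiplicity: "Bonferroni correction will be applied for multiple comparisons where appropriate". Neither the family of comparisons nor its size is given.

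Three visits recur in the plan. Primary outcomes sets the endpoint "at 3, 6 and 12 months compared with the one-month post-transplant baseline between the two groups". The Sample size section works "With 80% power and 95% confidence" on one difference in mean ALP and mentions no allowance for multiple testing.

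**The concern.** Single-step Bonferroni tests every comparison in a family of three at 0.05/3 = 0.0167. Holm tests the smallest p-value at 0.0167. If that is rejected, it tests the next at 0.025, and if that too is rejected, the last at 0.05. Both keep the family-wise error at or below 5% whatever the correlation, so repeated measurements on the same patients are no obstacle to either.

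Because Holm's first step is the Bonferroni test and its later thresholds are only looser, it cannot lose a finding that Bonferroni would make. What is at stake is power for the second and third findings in a family. That is relevant here because the plan looks at several visits to judge whether a response lasts, and because its sample size leaves no margin for a correction.

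**Working it through.** **Inputs from the protocol article.** Sample size section: "the difference in alkaline phosphatase (5.131 ± 39.639 vs 12.496 ± 52.139) was observed between the two groups"; 80% power; 5% error (two-sided assumed); 108 per arm. Allocation is 1:1.

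**Assumptions, not in the document.** A family of three tests (one per visit); the same effect at every visit that has one; correlation between the visit statistics of 0, 0.5 or 0.8.

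**Step 1: the plan's own figure.** Root-mean-square SD = √((39.639² + 52.139²)/2) = 46.31. Required n per arm = 2 × [46.31 × (1.960 + 0.842)/difference]².
- Difference as printed, 12.496 − 5.131 = 7.365: 621 per arm. This does not reproduce 108.
- Difference if the two values have opposite signs, 12.496 + 5.131 = 17.627: 108.4 per arm, close to the stated 108.

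I use 17.627 only as a scale that gives the 80% power the plan claims. The mismatch with the printed values is a separate matter.

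**Step 2: Bonferroni power by formula.** Standard error = 46.31 × √(2/108) = 6.302. Standardised effect = 17.627/6.302 = 2.797.
- Uncorrected: Φ(2.797 − 1.960) = 79.9%.
- Bonferroni, three tests: Φ(2.797 − 2.394) = 65.6%.

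**Step 3: Bonferroni against Holm by simulation** (500,000 draws per row, n = 108 per arm).

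| Visits with an effect | Correlation | Power per affected visit, Bonferroni | Holm | Gain (points) |
|---|---|---|---|---|
| 3 | 0 | 65.7% | 74.9% | 9.2 |
| 3 | 0.5 | 65.7% | 73.4% | 7.7 |
| 3 | 0.8 | 65.7% | 72.2% | 6.5 |
| 2 | 0 | 65.7% | 69.4% | 3.7 |
| 2 | 0.5 | 65.6% | 68.8% | 3.2 |
| 2 | 0.8 | 65.6% | 68.4% | 2.8 |
| 1 | 0 to 0.8 | 65.6–65.7% | 65.6–65.9% | 0.0–0.2 |

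With an effect at all three visits:
- Chance of at least one rejection: identical for both methods (96.0%, 87.3% and 79.4% at correlation 0, 0.5 and 0.8).
- Chance of rejecting all three: 28.3% against 49.3% at correlation 0, 41.6% against 59.0% at 0.5, and 51.2% against 65.7% at 0.8.

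**Step 4: error control.** With no effect anywhere, the family-wise error is the same for both: 4.9%, 4.4% and 3.5% at the three correlations. With an effect at one or two visits, Holm uses more of the allowance (at most 4.3%, against 3.3% for Bonferroni) and stays below 5%.

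**Step 5: a smaller effect.** With the printed difference of 7.365 at all three visits, power per visit is 11% with Bonferroni and 12 to 13% with Holm. Neither method rescues a trial that is too small for the effect.

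**The case against.** The strongest reply is that nothing here is wrong. Bonferroni is valid, easily prespecified and widely used, and the same remark could be made of any protocol that names it. That stands, and it is why this is a suggestion and not an error.

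A reader might infer more than the document supports:

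- *That the between-arm tests at months 3, 6 and 12 are held to 0.0167, so real treatment effects will be missed there.* The correction stands in the bullet on comparisons inside each arm and is qualified by a where-appropriate clause. The between-arm bullet names no correction. The primary endpoint is also a proportion of responders, so the figures above are not the plan's power for it.
- *That Bonferroni gives up power for no return.* It offers simple simultaneous confidence intervals that match its tests; Holm does not readily do so. The section plans no such intervals, so the loss is small, but it exists.
- *That correlated visits make Holm's advantage larger.* The table shows the reverse: 9.2 points at correlation 0 and 6.5 at 0.8. What drives the gain is a true effect at several visits, which is a different thing from correlated statistics.
- *That Holm is the right tool for a claim of durable response.* If that claim required significance at all three visits, each could be tested at 5% with no correction. Under the same assumptions this succeeds in 51.0%, 60.8% and 68.6% of trials at correlation 0, 0.5 and 0.8, slightly more than Holm.

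What survives all four is the dominance itself, which does not depend on which family is corrected.

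**Conclusion.** The point holds as a cheap improvement. For any family that the plan corrects, Holm keeps the 5% family-wise guarantee and is never less powerful than Bonferroni. The size is about 6 to 9 points per comparison if all three visits have an effect, 3 to 4 if two do, and practically none if one does. The probability of at least one finding is unchanged. These figures rest on a family of three, equal effects with 80% uncorrected power per test, and correlations from 0 to 0.8, none of which the article states. The dominance of Holm over Bonferroni needs none of them.

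**What to change.** In the third bullet of Statistical analysis, replace *Bonferroni correction* with *Holm step-down correction (family-wise 5%)*, for whichever family of comparisons the plan corrects. Do not word it so as to suggest that the between-arm tests are already corrected; including them would be a separate decision.

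The cost is a short edit to one sentence and no extra patients. Matching simultaneous intervals are less simple under Holm, so unadjusted 95% intervals would be shown beside Holm-adjusted p-values and labelled as such. The trial is open-label and still recruiting, so the change should be made by a dated amendment before any comparison of the arms.

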## Expected results

We expect a significant reduction in cholestatic liver enzymes following LDLT in the OCA group compared to the UDCA group, with improvements observed from one month to subsequent time points (3, 6, and 12 months). We hypothesize that the potent mechanism of action of OCA will ameliorate cholestatic injury and enhance graft survival. Additionally, we anticipate a reduction in biliary complications, all-cause mortality, and an increase in quality of life for OCA-receiving patients. This may reduce long-term financial expenditure for patients. Given that there are currently no drugs to prevent damage to the transplanted liver, a positive outcome could be a significant advancement for the transplant population. If beneficial, this study could lead to the adoption of OCA as a standard of care following liver transplantation. If proven beneficial, this study could support the potential adoption of obeticholic acid (OCA) as a therapeutic option in the management of post-liver transplant cholestasis. Although regulatory approval for OCA in primary biliary cholangitis was withdrawn due to the lack of confirmatory clinical benefit, its distinct mechanism of action and the different pathophysiological context of post-transplant cholestasis warrant independent evaluation in this setting.

## Conclusion

Although Ursodeoxycholic acid remains the standard first-line therapy, a substantial proportion of patients with post–liver transplantation cholestasis exhibit inadequate biochemical and clinical response, highlighting an important unmet therapeutic need. Obeticholic acid, a potent Farnesoid X receptor agonist, has demonstrated the ability to regulate bile acid synthesis, transport, and hepatobiliary homeostasis.

Given the unique pathophysiology of post-transplant cholestasis, this randomized controlled trial will evaluate the efficacy and safety of obeticholic acid in this population. We hypothesize that FXR activation will ameliorate cholestasis, improve graft function, and lead to better clinical outcomes.

### Confidentiality

All information about participants enrolled in this clinical trial are treated with the utmost confidentiality to protect their privacy and adhere to ethical standards. Personal identifying information are securely stored and accessible only to authorized personnel involved in the study. Data collected are anonymized and coded to maintain confidentiality during analysis and reporting. Any publication or presentation of results will not include identifiable information unless explicit consent is obtained from participants.

### Access to data

Access to data collected during this clinical trial will be managed according to established protocols and regulatory requirements. Authorized personnel, including investigators, statisticians, and regulatory authorities, will have access to raw data for analysis, monitoring, and verification. Data-sharing agreements will be established to govern access by external parties, ensuring compliance with data protection regulations and participant confidentiality. Requests for access to study data from external researchers or institutions will be considered on a case-by-case basis and subject to review by the study sponsor and relevant ethics committees.

